### Intervention

All participants will receive conventional medical care according to the regional guidelines and best practices. This consists of a brief instruction in exercises and pharmacologic management with the use of analgesics and anti-inflammatory agents and/or contact with a physiotherapist. The study’s additional occupational medicine intervention will last 3 months and include: 1) an initial consultation with the OP; 2) a workplace visit, if required; 3) a consultation with a physiotherapist; 4) a weekly telephone interview the first month and every second week the following two months with focus on adherence to the intervention plan; 5) midway interview with the OP with focus on return to/retention at work; 6) after three months a session with the OP evaluating the workplace-oriented intervention and the physical activity and concluding with further guidance. The intervention is illustrated in Figure 2.

**Figure 2 Fig2:**
[figure not shown]
The 12 weeks occupational medicine intervention.

#### The initial consultation with the OP

The aim of this consultation is to establish knowledge about the participant’s work situation and uncover opportunities to remove barriers for maintaining the participant in his job. A systematic interview will be performed and will comprise the following: 1) a detailed description of the participant’s daily work, including work function, work tasks, general work demand, work tasks that aggravate the back pain and organisational problems. 2) If there is a potential need for support for social problems such as job insecurity, advice will be given and registered. 3) Advice to the participant regarding actual level of physical activity will be given. The consultation takes approximately one hour and will result in an agreed intervention plan.

The intervention plan can include: 1) workplace visit; 2) advice concerning possibilities for more variation during the work day; 3) temporary or permanent ergonomic changes; 4) change of work tasks and job routines; 5) need for job training; 6) transfer to other job tasks; 7) rehabilitation or additional formal education; 8) a schedule for gradual return to work; 9) advice on avoiding work loads that aggravate the low back problems. If necessary this plan will be adjusted at the following telephone interviews. A short communication form is sent to the GP to prevent conflicting advice to the participant in the return to/retain at work process and, if necessary, the social authorities and employment exchange will be contacted.

#### Workplace visit

The workplace visit will be arranged in collaboration with the participant, the supervisor at the workplace and the occupational staff. Recommendations will be based on the active participation and strong commitment of both the participants and supervisor at the workplace. The aim of the workplace visit is to provide information for recommendations such as job rotations, the need for ergonomic initiatives, modifying the work, such as temporary or permanent exemption from special tasks and personal assistance. The recommendations for the job modifications and ergonomic changes are presented for the participants and the supervisor at the workplace and are reported in a structured scheme. The participant and the supervisor are responsible for implementing the plan.

#### Consultation with a physiotherapist

In addition to the occupational medicine plan, three 45-minute self-administered physical activity sessions a week are planned by a physiotherapist. The goal for these physical activities is that they should be easily integrated into the participant’s life style (for example, sports activities with the kids, swimming, fast walking, running, bicycling and the like).

#### Telephone interview

The participants are contacted by the physiotherapist weekly during the first month to ensure that the occupational and training plans are followed; if necessary, adjustments of the plan will be made. For the following two months the participants are contacted every 14 days.

#### Six weeks midway interview with the occupational staff

This interview will focus on the potential of the participants to stay at work; small necessary adjustments of the plan can also be made. This interview will last about 45 minutes.

#### Three months consultation with the OP

At this consultation the intervention period will be evaluated, and in cooperation with the participant a final conclusion concerning her professional future will be made. Participants who declare that they have not followed the intervention plan will be defined as non-adherent to the intervention. This consultation will last approximately one hour.

All intervention participants are encouraged to continue receiving healthcare for any non-back pain-related conditions from their usual primary care providers during the intervention.

### Primary outcome

The primary outcome of this study is retention at work after occupational medicine intervention, measured as the accumulated duration of self-assessed sick leave due to LBP over three and six months. The sick leave data is assessed weekly on a paper-based sick leave diary. The participants have to answer the following question: *How many days have you been on sick leave due to LBP during the past week?* For the first six months, all participants will weekly receive a text message with a reminder to answer the sick leave question in the diary. Additional participants can be contacted by telephone every second week, and the accumulated sick leave will be registered by an independent observer.

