**Methods/design:**

We will conduct a randomised controlled trial enrolling 300 participants with difficulty in maintaining physically demanding jobs due to low back pain for a current period of 2 to 4 weeks. Participants will be randomised and stratified according to their age and gender before being allocated in a 1:1 ratio to either control or additional occupational medicine intervention. Both groups will receive conventional treatment for their low back pain during the study. All participants will be thoroughly assessed for causes of low back pain and potential prognostic factors by questionnaires, clinical specialist assessments and magnetic resonance imaging (MRI) scans of the lumbar spine. Primary outcome is the accumulated duration of self-assessed sick leave (in days) due to low back pain during 6 months from baseline. Secondary outcomes include general self-rated back pain, disability and screening for potential prognostic factors: fear avoidance behaviour, disability, health status and degenerative MRI findings. For tertiary purposes selected outcomes will also be assessed after 1 and 2 years from baseline.

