## Methods/design

As illustrated in Figure 1, this is a randomised controlled trial with 1:1 allocation. It is conducted in accordance with the SPIRIT (Standard Protocol Items: Recommendations for Interventional Trials) 2013 guidelines [22]. The study is designed to investigate if an additional occupational medicine intervention can retain individuals with physically demanding jobs and LBP in gainful employment over a 6-month period. Eligible participants will be randomised after baseline measurements to one of two parallel groups: 1) control, 2) additional occupational medicine intervention. Data are collected at each stage of the trial, at initial telephone screening, allocation, occupational sessions and through all follow-up visits, and are reported according to CONSORT (Consolidated Standards of Reporting Trials) statements [23]. The study is approved by the Local Research Ethics Committee, Region H, Denmark (H-3-2013-161) 20 November 2013.

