### Secondary outcomes

Secondary outcomes will focus on sick leave and different aspects associated with LBP with the potential to affect the ability to return to/stay at work. Sick leave is additionally assessed by using data from the Danish National Register on Public Transfer Payments (Danish acronym DREAM). The DREAM register includes week-by-week records of any type of public transfer payment at an individual level. Sick leave periods of less than two consecutive weeks are not recorded in the DREAM register. Pain will be evaluated by using the 13-item painDETECT questionnaire, which includes measurements of LBP on an ordinal 11-point numerical rating scale (NRS: 0 = no LBP; 10 = worst LBP possible) [26]. The validated 24-item Roland Morris Disability Questionnaire will measure participant-rated LBP disability [27]. The participant’s work ability will be rated by three selected questions from the seven-item Work Ability Index questionnaire [28] and by an occupational standard baseline questionnaire collecting information on demographics, education level, leisure-time physical activity and the psychosocial work environment. General health status is collected with the Short Form Health Survey (SF-36) to assess changes in physical functional (SF-36 physical function subscale) and mental health (SF-36 mental health subscale) [29,30]. The psychosocial aspect of LBP will be measured with the validated Fear Avoidance Beliefs Questionnaire, a 16-item instrument measuring back-pain fears on two subscales related to physical activity and work which are rated from 0 (completely disagree) to 6 (completely agree) [31] [http://fysio.dk/fafo/Nyheder/Fear-Avoidance-Beliefs-Questionnaire]. Overall satisfaction with the intervention for the participants of this group is rated at each follow-up visit on an 11-point NRS with the anchors ‘not at all satisfied’ to ‘extremely satisfied’. The baseline MRI evaluation represents a descriptive outcome, and the lumbar degeneration is measured as a sum score of the discus at all lumbar levels [32,33].

If a participant is unable to attend the half-year visit in person, the primary outcome measures and a subset of secondary outcomes can be administered via paper-based questionnaires sent to the participant’s home with a stamped return envelope. All primary and secondary outcome assessments are also presented in Table 1.

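### The primary outcome is labelled retention at work but counts only low-back-pain sick-leave days, so on its own it cannot support a conclusion about staying in employment

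*Protocol article*

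**What the plan says.** The Methods/design section gives the aim as finding out whether the added intervention "can retain individuals with physically demanding jobs and LBP in gainful employment over a 6-month period". The Background states the objective in similar terms.

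The Primary outcome section defines the endpoint as "retention at work after occupational medicine intervention, measured as the accumulated duration of self-assessed sick leave due to LBP". Its single source is the weekly diary question "How many days have you been on sick leave due to LBP during the past week". The abstract agrees on the measure but omits the label: "Primary outcome is the accumulated duration of self-assessed sick leave (in days) due to low back pain during 6 months from baseline". The Statistics section puts the main analysis on sick leave after 6 months, by allocated group.

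Three other places matter:

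- **Inclusion criteria.** Everyone is employed at entry (about 30 hours a week or more) and worried about keeping the current job.
- **The initial consultation with the OP.** The intervention plan may include "rehabilitation or additional formal education; 8) a schedule for gradual return to work". The three-month consultation ends with a conclusion about the participant's working future.
- **Secondary outcomes and Table 1.** The DREAM register holds "week-by-week records of any type of public transfer payment at an individual level", but is cited as a further source on sick leave. Job category is recorded at baseline, 6 months, 1 year and 2 years, and at a telephone interview. Neither enters the primary outcome.

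**The concern.** Absence because of back pain and loss of employment are different events. A person who resigns, is dismissed, or moves to a pension or full-time education has no employer to be absent from. A literal answer to the diary question is then zero, which is the best weekly value, in the weeks when retention has failed.

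Such exits are foreseeable, because participants are selected for concern about keeping their job. They may also differ by arm. Rehabilitation and education are listed options only in the intervention plan, which could raise exits there. If the intervention works as intended, exits would instead be more common in the control arm, and the diary count would understate the benefit. Analysing participants as randomised does not remove this, because the discrepancy lies in what is counted. At stake is whether a result on the primary outcome can be reported as a result on retention.

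**Working it through.** **The plan's own figures.** Inputs from the Sample size section: difference 6 days, SD 17 days, two-sided 0.05, power 80%.

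- n per group = 2 × (1.960 + 0.842)² × 17² / 6² ≈ 126.0, rounded up to 127. The exact two-sample t-test gives 80.0% power at 127.
- With 150 per group the exact t-test gives 86.1%.

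Both stated figures reproduce. The arithmetic is sound, and the issue is what the days represent.

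**How exits enter.** Assumptions, none of them from the article: a 5-day working week; D working days after an exit that are days not at work but read as zero in the diary; SD of the diary count stays at 17. Take differences as control minus intervention, so that positive favours the intervention. Let p_C and p_I be the shares leaving employment. Then

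diary difference = difference in days not at work − (p_C − p_I) × D.

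For an exit midway through 26 weeks, D = 13 × 5 = 65.

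| Excess exits in control | Shift (days) | Share of 6-day target | Diary difference if the true difference is 6 days | Power, 150 per group |
|---|---|---|---|---|
| 0 points | 0 | 0% | 6.0 | 86.1% |
| 2 points | 0.02 × 65 = 1.3 | 22% | 4.7 | 66.5% |
| 5 points | 0.05 × 65 = 3.25 | 54% | 2.75 | 28.7% |

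In a group of 150, 2 points is 3 people (0.02 × 150) and 5 points is 7 or 8 (0.05 × 150 = 7.5). If the excess is in the intervention arm the sign reverses: with no true difference in days not at work, 5 points would show as an apparent benefit of 3.25 days.

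**Sensitivity to exit timing.** The whole 6-day difference is offset at an imbalance of 6 / D:

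- D = 32.5 (exit three-quarters through): 18.5 points
- D = 65 (midway): 9.2 points
- D = 130 (at the start): 4.6 points

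**Cost in variance of counting exits.** If a share q leaves midway in each arm, independently of other absence, SD = √(17² + q(1 − q) × 65²).

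- q = 2%: √(289 + 82.8) = 19.3, and power for 6 days at 150 per group is 76.6%.
- q = 5%: √(289 + 200.7) = 22.1, and power is 64.8%.

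This bears on the choice of remedy below.

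**The case against.** The strongest reply is that the operational endpoint is clear and consistent. The abstract, sample size and statistics sections all use sick-leave days; only the Primary outcome section adds the retention label, and it states the measure in the same sentence. Using sick leave as a disclosed marker of retention is a design choice, and how to score weeks after an exit is a rule that an article may leave to the full protocol or the SAP. That stands, so the absence of such a rule is not held against the article. What remains is the label and the aim: no later scoring rule makes a question about sick leave measure employment.

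Exits are also not invisible. Job category and DREAM would show many of them, and the planned cost analysis covers pensions, schooling and redeployment. This stands too, and makes the remedy cheap. The Cox analysis of time until return to work does not fill the gap: participants enter whatever their sick-leave status, and a return to work says nothing about later job loss.

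A reader might infer more than the article supports:

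- **That a leaver scores zero overall.** Sick-leave days before the exit still count. Even the later zeros are a literal reading of the question, not a stated rule: a leaver might leave the diary blank, or still be sick-listed.
- **That the trial would report the opposite of the truth.** This needs more exits in the intervention arm. The direction is unknown, and an intervention that works would be understated.
- **That part-day absence is lost.** Nothing in the diary question bars fractions of a day.
- **That the primary outcome must be redefined.** Recruitment was under way, the higher SD could take power below 80%, and counting every departure from the original job would score a move to suitable work elsewhere, or rehabilitation in the agreed plan, as failure.

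**Conclusion.** The point holds in a limited form. The primary outcome carries the name of one construct and measures another, and the diary count alone cannot support a conclusion about retention in gainful employment. The text shows this without any calculation.

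The size cannot be determined from the article, which gives no exit rate. The shift of 1.3 to 3.3 days (22% to 54% of the 6-day target) is an illustration that assumes mid-period exits, up to 65 hidden working days each, and a 2 to 5 point imbalance. It is an error relative to days not at work, not a bias in the count of sick-leave days as literally defined, and it can run either way. The sample size calculation is unaffected.

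**What to change.** 1. Keep the diary count as primary and call it LBP sick-leave days throughout.
2. Flag diary weeks that fall after a participant has left employment, and do not treat them as true zeros without that flag.
3. Report exits from employment by arm at 6 months.
4. Pre-specify a key supportive analysis of days not in gainful employment: LBP sick-leave days plus working days after leaving employment. A move to another job does not count as failure. State beforehand how weeks of rehabilitation or education are classified. Use the weekly DREAM records and the job-category item.
5. Limit any claim about retention to what that analysis supports.

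**Cost.** A change of wording and some added programming on data already planned; the primary endpoint and the sample size stay as they are. There are three drawbacks. Not every exit is due to back pain. Exits without a transfer payment do not appear in DREAM and can be dated only roughly from job category. The supportive measure has higher variance, so it will be less precise than the primary.

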### Secondary outcomes

Secondary outcomes will focus on sick leave and different aspects associated with LBP with the potential to affect the ability to return to/stay at work. Sick leave is additionally assessed by using data from the Danish National Register on Public Transfer Payments (Danish acronym DREAM). The DREAM register includes week-by-week records of any type of public transfer payment at an individual level. Sick leave periods of less than two consecutive weeks are not recorded in the DREAM register. Pain will be evaluated by using the 13-item painDETECT questionnaire, which includes measurements of LBP on an ordinal 11-point numerical rating scale (NRS: 0 = no LBP; 10 = worst LBP possible) [26]. The validated 24-item Roland Morris Disability Questionnaire will measure participant-rated LBP disability [27]. The participant’s work ability will be rated by three selected questions from the seven-item Work Ability Index questionnaire [28] and by an occupational standard baseline questionnaire collecting information on demographics, education level, leisure-time physical activity and the psychosocial work environment. General health status is collected with the Short Form Health Survey (SF-36) to assess changes in physical functional (SF-36 physical function subscale) and mental health (SF-36 mental health subscale) [29,30]. The psychosocial aspect of LBP will be measured with the validated Fear Avoidance Beliefs Questionnaire, a 16-item instrument measuring back-pain fears on two subscales related to physical activity and work which are rated from 0 (completely disagree) to 6 (completely agree) [31] [http://fysio.dk/fafo/Nyheder/Fear-Avoidance-Beliefs-Questionnaire]. Overall satisfaction with the intervention for the participants of this group is rated at each follow-up visit on an 11-point NRS with the anchors ‘not at all satisfied’ to ‘extremely satisfied’. The baseline MRI evaluation represents a descriptive outcome, and the lumbar degeneration is measured as a sum score of the discus at all lumbar levels [32,33].

If a participant is unable to attend the half-year visit in person, the primary outcome measures and a subset of secondary outcomes can be administered via paper-based questionnaires sent to the participant’s home with a stamped return envelope. All primary and secondary outcome assessments are also presented in Table 1.

**Table 1 Tab1:** **Protocol schedule of forms and procedures**

	**Baseline**	**6 months primary outcome**	**1 year**	**2 year**
The occupational medicine standard baseline questionnaires	X			X*
Job category ¶	X	X	X	X
Physically work load in current physically demanding job, Grading (1-4) ¶	X	X	X	X
Sick leave due to LBP the last year, days	X††	X†	X††	X††
Clinical examination	X	X	X	
Pain, VAS: (0-100 mm)	X	X	X	X
SF-36, score (0-100)	X	X	X	X
Work Ability Index Questionnaire 3 items	X	X	X	X
Fear Avoidance Beliefs, Work Subscale (0-42)	X	X	X	X
Fear Avoidance Beliefs, Physical Activity subscale (0-24)	X	X	X	X
Pain categorization, PainDETECT®, score (0-38)	X	X	X	X
Roland Morris Disability, score (0-24)	X	X	X	X
Magnetic resonance imaging, semi-quantitative scores	X		X	
Satisfaction with the intervention, NRS (1-10)		X	X	X

*Selected questions. †Sick leave due to LBP measured weekly during the first six months previously specified in the ’primary outcome‘ section. ††Patient-reported outcome. ¶ Additional reported at the telephone interview.

### Sample size

For a two-sample pooled *t*-test of a normal mean difference with a two-sided significance level of 0.05 (*P* < 0.05), assuming a common standard deviation of 17 days [17,34], a sample size of 127 participants per group is required to obtain a power of at least 80% to detect a mean difference of 6 days. Expecting some drop-outs during the trial period (less than 20%), it was decided for pragmatic reasons to enrol 300 participants in total (that is, 150 participants in each group). Including 300 participants in the intention-to-treat population, based on the assumptions above, corresponds to a statistical power of 86.1% to detect a mean difference of 6 days.

### Randomisation

The allocation occurs through a 1:1 ratio by a predetermined restricted randomisation scheme. The participants are stratified according to their age at enrolment (<40 years or ≥ 40 years) and gender (male or female). The eligible participants are randomly assigned in permuted blocks of 4 and 6, according to computer-generated random numbers, to be enrolled in either the intervention or control group. The randomisation is administered by predetermined sequentially numbered, opaque envelopes stored in a locked cabinet in a secure location. The randomisation is administered by Good Clinical Practice (GCP)-trained personnel not involved in the outcome measurement or the intervention.

### Blinding

The physicians performing the clinical examinations of the participants as part of the assessment of this trial are not taking part in occupational medicine intervention [23]. In addition, we will also try to make the physicians of assessment blinded for the allocation by instructing the participants not to mention their allocation in any follow-up visits. The OPs will, as coordinators of the study, not be blinded to the participant’s allocation but to the participant’s outcome data. The primary outcome is self-administered by a paper-based diary, and most of the secondary outcome measures are self-administered questionnaires on touch screen without involvement of the observers. In case of need of a telephone interview, this will be performed by personnel not connected to the intervention.

